### Questionnaire on Withdrawal Symptoms

During the study period, participants will be instructed to complete electronic questionnaires regarding withdrawal symptoms associated with the withdrawal of medication. The number of times and when the participant must complete the questionnaire is dependent on the allocated withdrawal method (Figure 1). The questionnaires can be completed with assistance from the parents.

**Figure 1 figure1:**
[figure not shown]
A detailed description and timeframe of how questionnaires on withdrawal symptoms should be answered regarding the applied withdrawal method.

### Randomization Procedure

Randomization will be performed in the REDCap (Research Electronic Data Capture, Vanderbilt University) portal and will occur centrally. An electronic case report form is built for the study data to be entered and for the randomization to be performed. Following written informed consent, randomization is stratified by a 1:1 allocation within each stratum using predefined block sizes for sites. Randomization is by a computer-generated random number list.

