### Statistical Analysis

Continuous variables will be presented as median with interquartile range for nonnormal distributed data, and as mean (SD) for normally distributed data. Categorical data will be presented as numbers and percentages. The distribution of data will be analyzed using histograms and QQ plots.

The hypothesis that gradual withdrawal is superior to abrupt withdrawal regarding the risk of recurrence of incontinence will be analyzed by logistic regression.

Two logistic regression models with different variations of adjustment. One logistic regression model with adjustment for each prescribed medication, as the randomization stratifies within the prescribed medication group. Another logistic regression model in which variables are adjusted due to suspicion of possible effect modification. The degree of adjustment will follow the event per the Variable rule. The logistic regression models will be analyzed at data of recurrence or not after 1 month, and hereafter 3, 6, and 12 months for a decreasing population who remain. Participants with recurrence of urinary incontinence will be described with descriptive statistics. The secondary outcome of side effects related to withdrawal will be presented with descriptive statistics.

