### Sample Size Calculation

To our knowledge, there is no available data regarding the efficacy of withdrawal strategies for pharmacological treatment with solifenacin or mirabegron in children diagnosed with urinary incontinence. Few studies have evaluated desmopressin withdrawal in children with enuresis. In the lack of alternatives, we have based our sample size calculation on these available desmopressin data, assuming a relapse rate of 40% with abrupt withdrawal of pharmacological treatment and 10% with gradual withdrawal of pharmacological treatment. With a significant level of .05 and a power of 80%, the minimal required sample size for adequate power is 64 participants in each group. We expect a maximum dropout rate of 10%. Therefore, 72 participants are included in the groups, for a total of 216 participants.

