### Strengths and Limitations

The strength of our study is the randomized multicenter design, encompassing 5 pediatric departments across Denmark. This ensures broad applicability and relevance in daily clinical practice. The study is embedded into and reflects daily clinical practice. The pragmatic design ensures the timely inclusion of patients and excludes participants with relapses of urinary incontinence.

The main limitation is the lack of blinding, which could introduce bias by influencing outcome assessment or potentially introducing placebo effects. Without blinding, investigators and participants are aware of withdrawal allocation, which can lead to biased behavior while answering the questionnaires and data interpretation. Another limitation is no background knowledge about socioeconomic factors.

By conducting the study in real-life settings with medication that is familiar to patients and parents, the findings are more likely to apply to clinical practice, as they reflect the challenges and circumstances encountered in routine medical care. Furthermore, patients are more likely to adhere to treatment protocols involving medications they are familiar with or have easy access to through standard prescriptions, increasing the feasibility of recruitment and retention in the study.

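### Site enters the blocked randomisation but is left out of the logistic model that adjusts for medication on the ground that randomisation is stratified by it (minor)

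*Protocol article*

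**What the plan says.** Under Randomization Procedure, the protocol article states that "randomization is stratified by a 1:1 allocation within each stratum using predefined block sizes for sites". The strata are not listed there. Trial Design and Visit 1 place the 1:1 allocation within each of three drug groups: solifenacin, mirabegron, or both. Strengths and Limitations describes a "randomized multicenter design, encompassing 5 pediatric departments across Denmark".

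Statistical Analysis gives two logistic regression models. The first is described as "One logistic regression model with adjustment for each prescribed medication, as the randomization stratifies within the prescribed medication group". The second adjusts for unnamed variables suspected of modifying the effect. The extent of adjustment is limited by an events-per-variable rule, for which no threshold is given. Neither model is called primary, and site is named in neither.

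Sample Size Calculation works from two proportions, "assuming a relapse rate of 40% with abrupt withdrawal of pharmacological treatment and 10% with gradual withdrawal of pharmacological treatment", and does not involve site.

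**The concern.** The plan adopts a sound principle, which is to adjust for what the randomisation stratifies on, and applies it to only one of the two factors that the article brings into the allocation. Blocking within site forces the arms to be nearly balanced there. That removes site differences from the true sampling variation of the treatment estimate. A model without site does not know this, so its standard error is too large for the design and the test rejects too rarely under the null.

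Five departments may well differ in case mix and in when a child is judged ready for withdrawal. If they do, the trial gives up some power when the treatment effect is smaller than planned. That is conceivable, because the planning rates are borrowed from desmopressin in enuresis for want of better data.

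**Working it through.** **1. The plan's own figures.** Inputs from Sample Size Calculation: 40% versus 10%, alpha 0.05 (two-sided assumed), power 80%. Pooled-variance formula without continuity correction, mean proportion 0.25:

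n per arm = [1.960 × √(2 × 0.25 × 0.75) + 0.842 × √(0.40 × 0.60 + 0.10 × 0.90)]² / 0.30² = (1.200 + 0.483)² / 0.09 ≈ 31.5, rounded up to 32.

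Two arms give 64 per drug group, which matches "the minimal required sample size for adequate power is 64 participants in each group". Then 64 / 0.9 = 71.1, rounded up to 72, and 72 × 3 = 216, which matches "72 participants are included in the groups, for a total of 216 participants". Site plays no part in any of these figures.

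**2. Set-up for the effect of site.** Completers: 216 × 0.9 ≈ 194, or 97 per arm. Two models were compared by simulation:

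- without site: logit P(recurrence) = intercept + arm + drug (2 terms)
- with site: the same plus site (4 fixed terms)

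The test is Wald, |estimate / SE| > 1.96. Assumptions not in the documents: equal drug groups with no drug effect on recurrence, site shares of 40/20/15/15/10%, blocks of 4 within site and drug, and a between-site SD of 0, 0.5 or 1.0 on the logit scale. Overall recurrence rates were held at the stated values. There were 3,000 trials per power setting and 6,000 per null setting. Monte Carlo standard errors are about √(0.8 × 0.2 / 3000) = 0.7 points for power near 80% and √(0.05 × 0.95 / 6000) = 0.3 points for type I error.

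**3. Results, 194 completers (without site / with site).**

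| Site SD (logit) | Type I error, 25% vs 25% | Power, 40% vs 22% | Power, 40% vs 10% |
|---|---|---|---|
| 0 | 5.0% / 5.2% | 77.7% / 78.4% | 99.9% / 99.9% |
| 0.5 | 3.9% / 4.6% | 77.9% / 80.4% | 99.9% / 99.9% |
| 1.0 | 3.3% / 5.4% | 79.9% / 86.1% | 100.0% / 100.0% |

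The planned effect is a log odds ratio of ln(0.10/0.90) − ln(0.40/0.60) = −1.79. The 40% versus 22% case is −0.86, less than half of that, and is an assumption made to show where site could matter. With 64 children at 40% versus 10% (the size of one drug group, drug terms kept), power is about 78% to 79% with or without site.

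**4. Mechanism.** Under the null at SD 1.0, the model without site reports an SE of 0.336 while its estimates vary with SD 0.318. That gap is the conservatism. Adding site raises the model SE to 0.375. At 40% versus 22% and SD 1.0, the mean log odds ratio moves from −0.886 (odds ratio 0.41) to −1.120 (0.33) and the SE from 0.325 to 0.373. The ratio rises from 0.886 / 0.325 = 2.73 to 1.120 / 0.373 = 3.00. Power improves because the site-conditional odds ratio lies further from 1, not because the SE shrinks.

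**5. Sensitivity.** A simulation of 216 children with log odds ratio −0.85 and 1,500 trials per setting gave power losses of 1.1, 4.9 and 6.6 points at SD 0.5, 0.8 and 1.0. Its type I error without site was 4.9%, 4.0% and 2.5%, against 6.1%, 4.7% and 5.3% with site. A further simulation of 194 completers put the loss at about 0.5 to 4 points at 40% versus 22%, with type I error without site of about 4% at SD 0.8 to 1.0. The direction is consistent; the size depends on the assumed site pattern.

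**6. Events per parameter.** Expected events at the planned rates: 97 × 0.40 + 97 × 0.10 ≈ 48. Arm plus two drug terms: 48 / 3 = 16. With four site terms: 48 / 7 ≈ 7.

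**The case against.** The strongest reply is that the article is condensed, the handling of centre is commonly left to the analysis plan, and the article does not establish as much as a reader might infer. Four stronger readings are tempting.

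- *The primary analysis ignores site.* The article labels neither model primary, and the second model's covariates are unnamed, so site could be among them.
- *Site within drug group is certainly the blocking scheme.* That is the natural reading, but the strata are not listed, and the sentence could mean only that block sizes were set per site. If site were not a stratum, the conservatism described here would not follow.
- *The trial is underpowered or its sample size is wrong.* The stated figures reproduce without reference to site, and nothing is lost at the planned effect.
- *The estimate is biased, or a false superiority claim becomes more likely.* An odds ratio nearer 1 without site reflects non-collapsibility, which makes it a different estimand. Any error in the test is conservative.

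The events-per-variable rule is also a plausible reason for leaving site out: about 7 events per parameter would fail a threshold of 10, although 10 is an assumption.

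All of this limits the point. What stands is the inconsistency. The article does more than stay silent on covariates: it fixes the covariate of one model and gives a reason that applies equally to site if site is a stratum.

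**Conclusion.** The point holds as a minor inconsistency. The medication-adjusted model follows the randomisation for medication and not for site, without explanation. If sites differ with a logit SD of 0.5 to 1.0, the cost is a type I error of about 3% to 5% rather than about 5%, and roughly 2 to 6 points of power at 40% versus 22%. Those sizes rest on an assumed site SD, assumed site shares, blocking within site and drug, and an effect smaller than planned. The documents give no information on between-site variation. If sites do not differ, the omission costs essentially nothing.

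**What to change.** In Statistical Analysis, add site to the medication-adjusted model, preferably as a random intercept, or as fixed effects with small sites pooled. State that factors used in the randomisation are exempt from the events-per-variable rule. List the strata under Randomization Procedure and say which model is primary, so that the match can be checked. If site is deliberately omitted, give the reason.

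The cost is a few sentences, with no change to sample size or conduct. The article reports 25 of 216 children included by February 2025; because the trial is open-label, the choice is best fixed before outcomes accumulate. There are two downsides. Four fixed site terms take events per parameter from about 16 to about 7, and the analyses at 3, 6 and 12 months use a shrinking population; the random intercept avoids the four terms, though a variance estimated from five sites will be imprecise. The reported odds ratio also becomes conditional on site and should be described as such.

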### Statistical Analysis

Continuous variables will be presented as median with interquartile range for nonnormal distributed data, and as mean (SD) for normally distributed data. Categorical data will be presented as numbers and percentages. The distribution of data will be analyzed using histograms and QQ plots.

The hypothesis that gradual withdrawal is superior to abrupt withdrawal regarding the risk of recurrence of incontinence will be analyzed by logistic regression.

Two logistic regression models with different variations of adjustment. One logistic regression model with adjustment for each prescribed medication, as the randomization stratifies within the prescribed medication group. Another logistic regression model in which variables are adjusted due to suspicion of possible effect modification. The degree of adjustment will follow the event per the Variable rule. The logistic regression models will be analyzed at data of recurrence or not after 1 month, and hereafter 3, 6, and 12 months for a decreasing population who remain. Participants with recurrence of urinary incontinence will be described with descriptive statistics. The secondary outcome of side effects related to withdrawal will be presented with descriptive statistics.

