### Withdrawal of Participants and Criteria of Discontinuation of Study

A study participant should be withdrawn from the study if at any time one of the following criteria applies:

Recurrence of incontinence during the course of the study (defined as >2 episodes of incontinence assessed by a 14-day calendar of incontinence episodes).It is the wish of the participant (or their parents or parental custody holder[s]) for any reason (withdrawal of informed consent).The discretion of the investigator is for safety reasons.Severe compliance with study procedure as described in the protocol, as judged by the investigator.The investigator judges it as necessary due to medical reasons.Participants with a condition or a situation that, in the investigator’s opinion, may put the participant at significant risk or may interfere significantly with the participant’s participation in the study.Participants with any other condition or situation that, in the investigator’s opinion, may be valid for discontinuation from the study.

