### Primary Outcome

The primary outcome measure is the recurrence of incontinence after 1 month after initiation of withdrawal of the physician-prescribed medication, assessed by a self-reported 14-day calendar of incontinence episodes. In addition, recurrence of incontinence after 3, 6, and 12 months after initiation of withdrawal will be measured.

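### The 3-, 6- and 12-month models include only children who have not yet recurred, so they do not estimate the effect of withdrawal strategy on recurrence by those visits; the 1-month primary comparison is unaffected

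*Protocol article*

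**What the plan says.** Under Primary Outcome, the protocol article states: "The primary outcome measure is the recurrence of incontinence after 1 month after initiation of withdrawal of the physician-prescribed medication". It then adds the later visits: "In addition, recurrence of incontinence after 3, 6, and 12 months after initiation of withdrawal will be measured".

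Under Statistical Analysis, the method is fixed: "The hypothesis that gradual withdrawal is superior to abrupt withdrawal regarding the risk of recurrence of incontinence will be analyzed by logistic regression". The models are run at 1 month, and "hereafter 3, 6, and 12 months for a decreasing population who remain". Children who have recurred leave the modelling: "Participants with recurrence of urinary incontinence will be described with descriptive statistics".

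Two other sections show who remains. Under Withdrawal of Participants and Criteria of Discontinuation of Study, the first ground for withdrawal is "Recurrence of incontinence during the course of the study (defined as >2 episodes of incontinence assessed by a 14-day calendar of incontinence episodes"). Under Strengths and Limitations, the design is said to be one that "excludes participants with relapses of urinary incontinence". The article states no cumulative, carried-forward or time-to-event analysis of all randomised children.

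**The concern.** Still being recurrence-free at 1 month is an outcome of the trial, and the trial's hypothesis is that the arm affects it. If gradual withdrawal works in the first month, the abrupt arm loses more of its recurrence-prone children before the 3-month model is fitted. The groups compared at 3, 6 and 12 months are then no longer the groups that were randomised. The adjustment for prescribed medication does not restore the balance.

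The later visits matter because they can show whether gradual withdrawal prevents recurrence or only postpones it. The question is a live one: by the Intervention section, medication in the gradual arm ends 14 days after that process begins, so at the day-30 visit this arm has been off drug for about 16 days and the abrupt arm for about 30. An analysis limited to those who remain can make a mere delay look like harm from gradual withdrawal. It can also hide a lasting benefit.

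**Working it through.** **1. Inputs from the protocol article.** Sample Size Calculation gives relapse rates of 40% (abrupt) and 10% (gradual), a significance level of .05, power of 80%, 64 per group, 10% dropout, 72 per group after inflation, and 216 in total. Trial Design gives 1:1 allocation within three drug groups.

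**2. The plan's own figure.** A two-sided test of 40% against 10% (pooled variance, no continuity correction) needs 32 per withdrawal arm, hence 64 per drug group, with power 0.806. Then 64/0.9 = 71.1, rounded up to 72, and 3 × 72 = 216. The figure reproduces if a group is a drug group with two arms. Pooled over drugs, that is 216/2 = 108 per arm, or 108 × 0.9 ≈ 97 after dropout.

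**3. Assumption on timing.** The article gives no time point for the 40% and 10%. They are placed at month 1 here. All later risks below are also assumptions, because the article gives none.

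**4. Who remains after month 1.** Abrupt: 97 × 0.6 ≈ 58. Gradual: 97 × 0.9 ≈ 87.

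**5. What the planned 3-month model compares.** Let F1 and F3 be the cumulative recurrence at 1 and 3 months. The risk among those who remain is (F3 − F1)/(1 − F1). Odds ratios (OR) are gradual versus abrupt, so values above 1 count against gradual. The abrupt arm is set at F3 = 50% throughout: (0.50 − 0.40)/0.60 = 16.7%, odds 0.20.

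| Gradual F3 | Gradual risk among those who remain | Planned OR | Randomised (cumulative) OR |
|---|---|---|---|
| 50% (pure delay) | (0.50 − 0.10)/0.90 = 44.4%, odds 0.80 | 0.80/0.20 = 4.0 | 1.0 |
| 30% (lasting benefit) | (0.30 − 0.10)/0.90 = 22.2%, odds 0.286 | 0.286/0.20 = 1.43 | (0.30/0.70)/(0.50/0.50) = 0.43 |
| 25% (larger benefit) | (0.25 − 0.10)/0.90 = 16.7%, odds 0.20 | 1.0 | (0.25/0.75)/(0.50/0.50) = 0.33 |

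By exact enumeration of the two-sided chi-square test, the pure-delay comparison (58 versus 87 children) is significant in 95.5% of trials although the 3-month risks are equal. In the second row, the comparison of 97 versus 97 randomised children has 81.5% power.

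**6. The same at 12 months.** Take cumulative recurrence of 40, 47, 51 and 55% (abrupt) and 10, 22, 31 and 40% (gradual) at 1, 3, 6 and 12 months. The randomised 12-month OR is (0.40/0.60)/(0.55/0.45) = 0.55. Among those who remain, the risks are (0.55 − 0.51)/0.49 = 8.2% and (0.40 − 0.31)/0.69 = 13.0%, OR 1.69.

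**7. Cases without reversal.** Suppose susceptibility varies between children (gamma frailty, variance 1 to 2) and each child's hazard is reduced by a constant factor throughout. The planned ORs at 3 to 12 months are then 0.25 to 0.38, against cumulative ORs of 0.17 to 0.19. The direction is right but the effect is attenuated. With a constant hazard ratio and no frailty, and a later hazard of 0.2 to 1 times the month-1 hazard, the planned OR is 0.17 to 0.20 against a cumulative 0.13 to 0.16.

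**8. What decides the direction.** With abrupt at 50%, the planned OR exceeds 1 only if gradual cumulative recurrence exceeds 0.10 + 0.90 × 0.167 = 25%.

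**The case against.** A reader might infer that the trial's main result is compromised. The documents do not support that. The primary time point is 1 month, its model is fitted before any child has been removed for a recurrence found at a follow-up visit, and the later visits are additional measures.

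A reader might also infer that the later odds ratios will point the wrong way. They need not. The reversed and null results in step 5 all assume that, after month 1, more new recurrences arise in the gradual arm than in the abrupt arm (40, 20 or 15 percentage points against 10). If the benefit persists at the individual level, the planned odds ratio keeps its direction.

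Nor does the article say that 40% and 10% are 1-month rates. The split of 58 and 87, and every odds ratio above, rests on placing them there.

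The best defence of the plan is that risks among children still at risk are legitimate quantities: they are the building blocks of a discrete-time survival model. That is true, but the article describes no such model. It repeats separate logistic models on shrinking sets, under a hypothesis about the risk of recurrence, and a single interval's odds ratio does not answer that hypothesis for 3, 6 or 12 months. These points limit the size and reach of the concern but do not remove it.

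**Conclusion.** The point holds for the 3-, 6- and 12-month analyses only. The analysis set is stated, not merely left open, and it conditions on a post-randomisation outcome, so the resulting odds ratios do not estimate the effect of withdrawal strategy on recurrence by those visits. The possible error ranges from modest attenuation to reversal. It depends on when recurrences occur and how much susceptibility varies between children, neither of which the article gives. This should be fixed, because the later visits are the trial's evidence on prevention versus delay. It does not threaten the 1-month conclusion.

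**What to change.** Replace the clause on the later time points with wording such as:

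*At 3, 6 and 12 months, the outcome is cumulative recurrence detected by that visit, analysed in all randomised children with the same adjustment as at 1 month. A child recorded as recurred at an earlier visit counts as recurred at every later visit.*

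The word *detected* is needed because recurrence is read from a 14-day calendar before each visit, not observed continuously.

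Add a rule for children who leave without recurrence, since the article allows up to 10% dropout and lists several other withdrawal grounds. Examples are censoring at the last completed visit in a discrete-time or interval-censored time-to-recurrence model, or multiple imputation for the cumulative analysis. Either the cumulative analysis or the time-to-recurrence model is enough. Label any analysis restricted to those who remain as descriptive.

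The cost is analysis wording. Relapsed children need no further follow-up for this outcome, because a recorded recurrence already settles their later cumulative status. The article reports 25 of 216 children included as of February 2025 and expects recruitment to run until December 2027, so on that schedule the change can be made well before the later outcomes are analysed.

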## Methods

### Trial Design

This is an open-label, prospective randomized trial, allocating participants to each of the 3 pharmaceutical groups, according to the physician-prescribed medical treatment that the child is receiving (solifenacin, mirabegron, or solifenacin in combination with mirabegron; Textbox 1). Within each pharmaceutical group, the participant will be randomized 1:1 to the intervention being compared: either abrupt withdrawal or gradual withdrawal. The study duration for each participant will be 12 months and encompasses 1 virtual meeting and 4 follow-up phone consultations.

Overview of the pharmaceutical groups, according to the physician-prescribed medical treatment.

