### Secondary Outcome

Secondary outcome measures are as follows. Development of symptoms occurring after abrupt withdrawal of the prescribed medication (solifenacin or mirabegron), assessed by self-reported questionnaires on listed symptoms, as a change from baseline up to 30 days after initiation of withdrawal. Development of symptoms occurring after gradual withdrawal of the prescribed medication (solifenacin or mirabegron), assessed by self-reported questionnaires on listed symptoms, as the change from baseline up to 44 days after initiation of withdrawal. Refer to the Multimedia Appendix 1 for the listed symptoms. The questionnaires are constructed by the authors and do not validate or apply CHERRIES (Checklist for Reporting Results of Internet E-Surveys) items.

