### Ethical Considerations

#### Overview

The study is authorized by the authorities of the Danish Medicines Agency and the Danish Health Research Ethics Committee and registered at Clinical Trials in the European Union (EU CT 2023-510280-35-00). To our knowledge, no studies have been performed investigating the potential outcomes of abrupt versus gradual withdrawal of solifenacin or mirabegron used by children diagnosed with urinary incontinence. To our knowledge, no literature has assessed the connection between the abrupt withdrawal of antimuscarinic drugs and the development of withdrawal syndrome in children with urinary incontinence.

All pharmacological side effects will be handled in accordance with Danish legislation. No risk or unknown side effects are expected from medical treatment or withdrawal. The therapeutic potential for future patients justifies the project to be carried out. Participation in this study will not lead to any disadvantages for the patient in their treatment.

The study will be conducted in accordance with the protocol, applicable regulatory requirements according to Good Clinical Practice, and the ethical principles of the Declaration of Helsinki. Information regarding the participants is protected and anonymized according to the General Data Protection Regulation and the actual law. The study participants and their families will not be economically compensated for participating in the study.

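### Withdrawal symptoms are defined as two one-arm changes over unequal windows and only described, so the randomised abrupt-versus-gradual contrast for symptoms has no planned estimate or interval

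*Protocol article*

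**What the plan says.** The Trial Design section states the randomised comparison: "Within each pharmaceutical group, the participant will be randomized 1:1 to the intervention being compared: either abrupt withdrawal or gradual withdrawal". The pharmaceutical groups are solifenacin (1), mirabegron (2) and the combination (3).

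The Secondary Outcome section does not carry that comparison over to symptoms. Its first outcome is "Development of symptoms occurring after abrupt withdrawal of the prescribed medication (solifenacin or mirabegron), assessed by self-reported questionnaires on listed symptoms", measured "as a change from baseline up to 30 days after initiation of withdrawal". Its second is the counterpart for gradual withdrawal, measured "as the change from baseline up to 44 days after initiation of withdrawal". The Questionnaire on Withdrawal Symptoms section adds that the number and timing of questionnaires depend on the allocated method; the schedule is in Figure 1, which is not shown.

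The Statistical Analysis section gives logistic regression to recurrence and then says of symptoms: "The secondary outcome of side effects related to withdrawal will be presented with descriptive statistics".

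Two other places matter. The Safety section provides for registration of adverse events and reactions, including serious ones. The ethics overview notes that "no literature has assessed the connection between the abrupt withdrawal of antimuscarinic drugs and the development of withdrawal syndrome in children with urinary incontinence".

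**The concern.** A change from baseline within one arm mixes the effect of withdrawal with symptoms the children would have reported anyway. Randomisation removes that ambiguity, but only if the arms are compared. Here the outcome itself is split by arm, so the comparison is not the stated target, and the analysis sentence adds neither a difference nor a measure of its uncertainty.

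The article expects its results to influence withdrawal strategy. As planned, recurrence would enter that judgement as a modelled comparison, while symptom burden would enter as two separate descriptions over different lengths of time. A reader would set them side by side anyway, and the longer window in the gradual arm can create a difference by itself.

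**Working it through.** **1. The plan's own figure.** The Sample Size Calculation section assumes relapse of 40% (abrupt) and 10% (gradual), significance level .05 and power 80%. Taking the test as two-sided without continuity correction (sidedness is not stated):

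n per arm = [1.96·√(2·0.25·0.75) + 0.8416·√(0.4·0.6 + 0.1·0.9)]² / 0.30² = (1.200 + 0.483)² / 0.09 = 31.5, so 32.

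That gives 64 per medication group; 64/0.9 = 71.1, so 72; and 3 × 72 = 216. The figure reproduces, but it concerns recurrence. No rate or size is stated for symptoms, so every symptom rate below is an assumption.

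**2. Numbers available for a symptom contrast.** Assume equal medication groups of 72 and 10% dropout.
- All groups: 216 × 0.9 / 2 ≈ 97 per arm.
- Solifenacin-containing groups (1 and 3): 144 × 0.9 / 2 ≈ 65 per arm.
- Mirabegron alone (2): 72 × 0.9 / 2 ≈ 32 per arm.

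**3. Precision.** Half-width = 1.96·√[p₁(1−p₁)/n + p₂(1−p₂)/n]. With equal rates in both arms, in percentage points:

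| Assumed rate | 97 per arm | 65 per arm | 32 per arm |
|---|---|---|---|
| 10% | 8.4 | 10.3 | 14.7 |
| 20% | 11.3 | 13.8 | 19.6 |
| 30% | 12.9 | 15.8 | 22.5 |

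With 30% v 15% at 65 per arm: 1.96·√[(0.21 + 0.1275)/65] = 14.1 points.

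**4. Effect of the unequal windows.** The lengths have a rationale: 14 taper days + 30 = 44, so each window ends 30 days after complete cessation. Counted from initiation, they still differ by 14 days. With the same constant hazard in both arms, R₄₄ = 1 − (1 − R₃₀)^(44/30):

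| Risk by day 30 | Risk by day 44 | Spurious abrupt-minus-gradual difference |
|---|---|---|
| 5% | 7.2% | −2.2 points |
| 10% | 14.3% | −4.3 points |
| 20% | 27.9% | −7.9 points |

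A constant hazard is a simplification, and early-peaking symptoms would give a smaller distortion. Under it, the error favours abrupt withdrawal. Differing questionnaire counts could shift the difference further.

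**5. Conditional dilution.** If results were pooled over drugs, and if an excess under abrupt withdrawal occurred only with solifenacin-containing treatment, the pooled excess is d × (1 − m), where m is the mirabegron-only share. With d = 15 points and m = 1/3, it is 10 points. For example, 30% v 15% in groups 1 and 3 and 10% v 10% in group 2 give (0.60 + 0.10)/3 = 23.3% v (0.30 + 0.10)/3 = 13.3%. With m = 20% it is 12 points; with m = 50%, 7.5 points.

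**The case against.** Descriptive reporting of a secondary, unpowered safety outcome is a legitimate choice, more so with a questionnaire built by the authors and not presented as validated. The stated objective and hypothesis concern recurrence only. Intervals and subgroup displays are often left to an analysis plan, and none is shown here. If symptoms are tabulated as numbers and percentages by arm, a reader could compute a crude difference.

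Much of this stands: descriptive tables are not an error in themselves, and an unseen plan may add detail. It does not remove the point, because the article does more than stay silent. It fixes the outcome as two one-arm changes, fixes different windows for them, and names the type of analysis. A crude difference computed from such tables would carry the window problem shown above.

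Three stronger readings are tempting and not supported:
- *The questionnaire is the only systematic harm measure.* The Safety section also registers adverse events and reactions. The questionnaire is only the sole harm measure named as an outcome.
- *Symptoms will be pooled over drugs, so an antimuscarinic effect will be diluted.* Naming both drugs in the outcome does not prescribe pooling. A table by medication group and arm would fit the text equally well.
- *The ethics overview declares an antimuscarinic withdrawal syndrome to be the harm of concern.* It reports a gap in the literature, and the same section says no risk is expected from withdrawal.

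**Conclusion.** The point holds in a limited form. For withdrawal symptoms, the randomised contrast is neither the defined outcome nor planned to be estimated with any uncertainty, and the unequal windows make an informal comparison unreliable. The primary analysis is unaffected.

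An overall interval of about ±8 to ±13 points is attainable at the planned size, assuming symptom rates of 10% to 30%, equal medication groups and 10% dropout. Within drug groups it would be about ±14 points (30% v 15%, solifenacin-containing) and ±15 points (10% v 10%, mirabegron alone), and wider for mirabegron alone at higher rates. The one-third dilution applies only if results are pooled, the medication groups are equal and the effect is confined to solifenacin-containing treatment. It is a reason to show the estimate by drug, not an established defect.

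**What to change.** In Secondary Outcome, replace the two one-arm outcomes with one between-arm outcome: new or worsened listed symptoms relative to baseline, over windows of equal length with a stated anchor, using questionnaire time points common to both arms. One option is days 0–30 from initiation in both arms, supported by an analysis of the 30 days from complete cessation (days 0–30 abrupt, days 14–44 gradual). Both are useful because neither anchor is neutral: the first gives the gradual arm only 30 − 14 = 16 days after cessation, and the second omits its taper period. Check both against the schedule in Figure 1. State also how children withdrawn from the study at recurrence are counted, since the gradual window to day 44 runs past the day-30 visit.

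In Statistical Analysis, report the abrupt-minus-gradual risk difference with 95% CI, stratified by prescribed-medication group. Show it also for the solifenacin-containing groups (1 and 3) and for mirabegron alone (2), labelled as estimation without a significance claim. Keep the descriptive table of each symptom.

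The cost is mainly wording, provided Figure 1 already contains common time points; if not, the questionnaire schedule would need alignment. No dose or clinical rule changes. With 25 of 216 children included by February 2025, prespecification is still credible. The downsides are wide within-drug intervals and an estimate reported without multiplicity control.
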